#### Control arm

Patients randomized to the control arm will receive daily DOT provided by a peripheral health facility close to their residence. Under the DOT programme, patients report to the nearest DOT provider facility daily and drug intake is observed. On each visit, the TB card is ticked off in correspondence with the number of days they made a visit to the health centre and this card is retained at the health facility. At the monthly visits, the TB card is taken to the central MDR treatment facility for review by the managing clinician. At this point, the study team will record the number of doses taken/missed according to the TB card. Participants will receive adherence counselling on all routine visits at the central facility (Table 1).

### Allocation concealment mechanism

The designing of the randomization sequence within the Redcap tool was performed by a biostatistician who is blinded from the participant enrolment activities. The variables used to design the randomization sequence included gender and age group. At the stage of enrolment, the randomization is conducted in real time on the Internet-enabled Redcap tool by the member of the study team conducting the enrolment. The study team have no control over the randomization sequence.

### Allocation implementation

The study team (medical officer and or study nurse) having determined participant eligibility enter the participant gender and age into the automated randomization sequence within the Redcap tool and click a button to determine study allocation and or study arm in real time.

### Blinding (masking)

Given the nature of the intervention (a visible medicine box and the requirement not to report to a DOT facility daily), it was not feasible to blind study participants, primary care providers, the study team and or the data manager.

### Data collection plan

All participants will be reviewed by the study team monthly during routine visits (Table 3). On the initial visit, participants will be taken through a screening questionnaire to assess eligibility. Patients found to be eligible will then be taken through the informed consent process in the language of their preference. Enrolled participants will provide demographic information including age and gender. At each monthly study visit, participants will be taken through an interviewer-led questionnaire to capture clinical history (reported adverse events, treatment outcomes) and adherence information (adherence data downloads from MEMS devices, adherence data from TB treatment cards, pills counts, and participant-reported adherence on days of treatment missed). Adherence data will be used to provide tailored counselling for each participant to encourage treatment completion and this data will be shared with the participant’s primary clinician.

**Table 3 Tab3:**
[figure not shown]
Description of study procedures

^*^Drug susceptibility testing: sputum culture and sputum DST will be provided as standard of care by the health facility

## Laboratory assessments

Blood sampling to measure the concentrations of bedaquiline and linezolid will be conducted on months 2, 8 and 11 of treatment. Drug intake on the days for blood sampling will be performed by DOT and blood samples taken off prior to drug intake and 1-h post-drug intake. The blood samples will be placed in cooler boxes and transported to the laboratory on dry ice for samples from Lira Hospital and in a cooler box for samples from Mulago Hospital, processed and stored at −4 to −80 °C. Pharmacokinetic analysis will be performed at the Infectious Diseases Institution (IDI) translation laboratory. Quantification of the drug concentrations will be performed in batches using validated high-performance liquid chromatography (HPLC) and mass spectrometry at the Translation Laboratory of the Infectious Diseases Institute, Makerere University using MS.

Sputum smears and cultures will be performed as part of routine care and testing conducted at the government reference laboratory.

The study follow-up duration will be 24 months to cater for patients on both short- and long-term oral MDR-TB therapy. Treatment duration will be approximately 9 to 18 months: 9 months for participants that qualify for shorter MDR-TB/RR-TB treatment regimen and 18 months for those selected for the longer MDR-TB/RR-TB treatment regimen.

To ensure data quality, study information is captured with an e-questionnaire in Redcap that has been designed to send real-time notifications for inputted variables that may be out of range. The tool also does not accept for the person collecting data (medical officer and or study nurse) to verify the tool, but is redirected to the study coordinator and Data Manager to do the final verification for correct and missing data. In addition, the entire study team was trained afore on the use of the study Redcap tool and on other study-related standard operating procedure manuals including the collection of blood specimens for continued reference. In the event of a protocol violation, retraining on study protocol and procedures will be conducted.

### Retention of study participants in the Trial

For all persons approached to participate in the study, full information will be provided about the trial its aims, study procedures and duration. Participants will be given an opportunity to ask any questions they may have at the time of consent and any other time of the study. Data from participants that have withdrawn and or been withdrawn from the study will be retained for sub-analysis. All participants that have been withdrawn from study participation will be replaced to ensure the sample size is achieved.

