## Interventions: modifications

Participants may withdraw from the study at any time at their own request, or they may be withdrawn at any time at the discretion of the investigator or sponsor for safety or behavioural reasons, or the inability of the subject to comply with the protocol required schedule of study visits or procedures. Patients who are withdrawn at any time of the study may be replaced.

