### Statistical: outcomes

#### Adherence assessment

The primary outcome is the overall adherence rates among MDR-TB patients on self-administered therapy and on DOT. For the participants on the intervention arm, opening of the devices will be equated to a patient swallowing their medication and adherence will be derived from the number of days the device was opened as a proportion of the total number of days in the entire period of their MDR-TB treatment. Patients on the intervention arm will be required to take no less than 70% of their medication to be considered as having good adherence. For participants on the control arm (DOT), adherence information will be obtained from their TB treatment cards. Adherence rates will be calculated from the number of days that they report to the DOTS facility as a proportion of the total number of treatment complaint days in the entire period of their MDR-TB treatment. Participants who take their medication at least 80% of the time (missing no more than 5 days each month) will be considered as having good adherence.

The primary analysis will be a comparison of overall adherence in each arm. Adherence by self-administration (proportion of expected openings of the MEMS devices) and DOT (proportion of DOT visits) will also be compared at 2 months and 6 months in the intervention and control arms. The chi-square test and 1-way analysis of variance models will be used to compare outcomes by randomization arm. We shall use independent samples *t*-test to test for statistical difference mean adherence rates in the patient in the intervention and control arms. We will use an intent-to-treat approach (analysed all participants regardless of drug refills) to compare adherence outcomes by randomization arm using a generalized estimating equations model using repeated measures with identity link, exchangeable correlation structure and robust variance estimates.

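### Withdrawn participants are replaced and their data kept for a sub-analysis, which conflicts with intention-to-treat and can bias an open-label comparison of adherence

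*Protocol article*

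**What the plan says.** Four statements in the protocol article bear on this.

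- *Interventions: modifications* sets the grounds for withdrawal. Besides leaving at their own request, participants can be taken out by others: "withdrawn at any time at the discretion of the investigator or sponsor for safety or behavioural reasons, or the inability of the subject to comply". The compliance in question is with study visits and procedures. On replacement the section says: "Patients who are withdrawn at any time of the study may be replaced".
- *Retention of study participants in the Trial* is firmer on replacement: "All participants that have been withdrawn from study participation will be replaced to ensure the sample size is achieved". On the data it says: "Data from participants that have withdrawn and or been withdrawn from the study will be retained for sub-analysis".
- *Adherence assessment* defines the outcome: "The primary outcome is the overall adherence rates among MDR-TB patients on self-administered therapy and on DOT". It also sets the approach: "We will use an intent-to-treat approach (analysed all participants regardless of drug refills) to compare adherence outcomes by randomization arm".
- *Additional analyses and handling of missing data* names loss to follow-up as one route to a missing outcome, relies on a missing-at-random assumption within the GEE model, and adds an analysis with imputed primary outcomes.

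*Blinding (masking)* states that neither participants nor study staff are blinded. *Intervention arm*, *Control arm* and *Data collection plan* have the study team review device or TB-card adherence every month.

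**The concern.** If a withdrawn participant still counted towards the 164, nobody would have to be replaced to reach that number, and the data would not need a separate sub-analysis. Read together, the two sentences in the retention section put withdrawn participants outside the main analysis set, while the statistical section analyses everyone. A reader cannot tell who is in the primary comparison. The article is also inconsistent on whether replacement is optional or automatic.

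This matters more than usual because the outcome is adherence. On DOT it is measured by facility attendance. On self-administration it comes from devices read at monthly visits. Someone who cannot keep to visits or procedures may well be someone with poor adherence, and the staff who decide on withdrawal know both the arm and the adherence record. Substituting such people with new enrollees can change the arms differently, and the result would no longer estimate the difference between the groups as randomised.

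**Working it through.** **Reading the passages together.** The retention section gives sample size as the reason for replacement. Replacement serves that purpose only if the withdrawn person no longer counts. *Adherence assessment* counts all participants. Both cannot govern the primary analysis. The missing-at-random handling does not settle it: that handling applies to people who stay in the analysis set with incomplete data, not to people whose place has been given to someone else.

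**The loss allowance.** *Sample size* states 164 with 20% loss to follow-up. Taken at face value, 164 × 0.8 = 131 participants are expected to be evaluable, so replacing withdrawals to hold 164 allows for attrition a second time. One caution applies: 82 per arm does not follow from all the stated inputs together. For 70% versus 89%, two-sided 5%, power 0.9 and 20% loss, the result is 117 per arm. One route that does reach 82 (non-inferiority at 77.9%, margin 19%, one-sided 5%, power 0.9) includes no inflation for loss. The allowance is stated, but it cannot be confirmed that it is in the number.

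**Illustration of the bias.** The article gives no withdrawal rates, so the rates here are assumptions. Only the −10 point margin, the 95% interval and 82 per arm are taken from the article. Adherence is treated as a yes/no outcome.

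- True good adherence: 60% on self-administration, 70% on DOT, so the true difference is exactly −10 points.
- *w* = proportion of an arm withdrawn and replaced; *a* = proportion of those withdrawn who were good adherers; replacements behave like those who remain.
- Apparent rate: p* = (p − w·a)/(1 − w).
- SE = √{[p*_S(1 − p*_S) + p*_D(1 − p*_D)]/82}.
- Probability of declaring non-inferiority = Φ[(p*_S − p*_D + 0.10)/SE − 1.96].

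Worked case, 10% withdrawn on self-administration only, all non-adherers: p*_S = 0.60/0.90 = 0.667 and p*_D = 0.70. SE = √[(0.222 + 0.210)/82] = 0.0726. Then (−0.033 + 0.10)/0.0726 = 0.92, and Φ(0.92 − 1.96) = 0.149.

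| w, self-adm. | w, DOT | a | Apparent rates | Apparent difference (points) | P(non-inferiority declared) |
|---|---|---|---|---|---|
| 0 | 0 | – | 60.0% vs 70.0% | −10.0 | 2.5% |
| 5% | 0 | 0 | 63.2% vs 70.0% | −6.8 | 6.3% |
| 10% | 0 | 0 | 66.7% vs 70.0% | −3.3 | 14.9% |
| 10% | 0 | 20% | 64.4% vs 70.0% | −5.6 | 8.8% |
| 15% | 5% | 0 | 70.6% vs 73.7% | −3.1 | 16.5% |
| 15% | 5% | 20% | 67.1% vs 72.6% | −5.6 | 9.0% |
| 20% | 0 | 0 | 75.0% vs 70.0% | +5.0 | 57.7% |
| 10% | 10% | 0 | 66.7% vs 77.8% | −11.1 | 1.7% |
| 5% | 15% | 0 | 63.2% vs 82.4% | −19.2 | below 0.1% |

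More withdrawal of non-adherers on self-administration pushes towards non-inferiority. Equal withdrawal slightly widens the gap. The reverse imbalance works strongly against the intervention.

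**The case against.** The best defence is that no sentence says withdrawn participants leave the primary analysis. The retention section says their data are retained, and it can be read as recruiting extra patients on top. The statistical section plainly says intention-to-treat and provides for missing outcomes. In a condensed article the sub-analysis may be defined in a document not shown. That stands to this extent: exclusion is an inference, though a strong one, since replacement to achieve the sample size has no purpose otherwise.

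Secondly, a reader might infer that staff withdraw people because of poor adherence. The article does not say that. The stated ground concerns study visits and procedures, the stated response to poor adherence is tailored counselling, and daily DOT attendance at a peripheral facility is distinct from the monthly study visit. What remains is that behavioural reasons are open-ended and nothing limits discretionary withdrawal to reasons unrelated to adherence. The link is possible and unguarded, not established.

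Thirdly, enrolling more randomised patients does not itself bias anything; only leaving out those already randomised does. That is correct, and the fix respects it.

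**Conclusion.** The replacement and sub-analysis wording conflicts with the intention-to-treat statement, and the optional and automatic versions of the replacement rule conflict with each other. Under the natural reading, the primary comparison would omit people for reasons that can depend on the outcome, in a trial whose staff are unblinded.

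A reader might conclude that replacement always pulls the difference towards zero and so favours non-inferiority. The documents do not support that. It holds only if more non-adherers are withdrawn on self-administration than on DOT. With equal 10% withdrawal of non-adherers, a true −10 points appears as −11.1. The size is also unknown, because no withdrawal rates are given. The rise from 2.5% to about 15% rests on the assumed 60% and 70%, on all those withdrawn being non-adherers, and on withdrawal in one arm only. If a fifth of them were good adherers, the figure is 8.8%. What can be said firmly is that the rule leaves error control dependent on a discretionary process, and that its most harmful case is the one a non-inferiority trial must guard against.

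**What to change.** Reconcile *Interventions: modifications*, *Retention of study participants in the Trial* and *Adherence assessment*:

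1. Delete replacement as substitution from both sections where it appears.
2. State that every randomised participant stays in the primary analysis in the assigned arm, whatever the reason for withdrawal. The grounds for withdrawal from the study need no change for this purpose; they simply must not determine who is analysed.
3. State that, where consent allows, TB-card, device and programme outcome data continue to be collected after a participant stops study visits.
4. Count anyone enrolled after a withdrawal as an additional randomised patient, analysed alongside the person who withdrew. *Trial status* reports enrolment at 70%, so some may already have been enrolled on this basis.

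The cost is a short amendment and matching wording in the analysis plan, with no change to the stated 164. The number with complete data may be slightly lower. The stated 20% allowance is meant to cover that, subject to the caution above that the allowance cannot be confirmed from the stated inputs.

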### Data management

Clinical data will be entered into a study-specific database by trained designated study staff on a regular basis from completed Case Record Forms (CRF) using Redcap. Information will primarily be captured using Redcap and CRFs will be printed out for filing and storage. Case Record Forms and other source documents will be kept in locked cabinets. No participant-identifying information will be disclosed in any publication or at any conference activities arising from the study. The participant data captured in the Redcap tool will be accessed in real time by the data manager, who will provide data queries for the study team to address. In addition, the Redcap data collection tool has been fashioned to generate automated checks on entry of certain variables that are out of range. Data management procedures are detailed in the standard operating manual.

### Statistical: outcomes

#### Adherence assessment

The primary outcome is the overall adherence rates among MDR-TB patients on self-administered therapy and on DOT. For the participants on the intervention arm, opening of the devices will be equated to a patient swallowing their medication and adherence will be derived from the number of days the device was opened as a proportion of the total number of days in the entire period of their MDR-TB treatment. Patients on the intervention arm will be required to take no less than 70% of their medication to be considered as having good adherence. For participants on the control arm (DOT), adherence information will be obtained from their TB treatment cards. Adherence rates will be calculated from the number of days that they report to the DOTS facility as a proportion of the total number of treatment complaint days in the entire period of their MDR-TB treatment. Participants who take their medication at least 80% of the time (missing no more than 5 days each month) will be considered as having good adherence.

The primary analysis will be a comparison of overall adherence in each arm. Adherence by self-administration (proportion of expected openings of the MEMS devices) and DOT (proportion of DOT visits) will also be compared at 2 months and 6 months in the intervention and control arms. The chi-square test and 1-way analysis of variance models will be used to compare outcomes by randomization arm. We shall use independent samples *t*-test to test for statistical difference mean adherence rates in the patient in the intervention and control arms. We will use an intent-to-treat approach (analysed all participants regardless of drug refills) to compare adherence outcomes by randomization arm using a generalized estimating equations model using repeated measures with identity link, exchangeable correlation structure and robust variance estimates.

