#### Additional analyses and handling of missing data

Interim data analysis will be conducted once 50% of the overall sample size has been achieved with the purpose of guiding the data monitoring board on recommendations for the study. Missing data will be dealt with as missing covariate and outcome data. As a generalized estimating equations model will be used, missing outcome data will be dealt with using a missing at random assumption. If > 3% of data for covariate data is missing, multiple imputation will be used for the primary analysis. Given the way the adherence rate is computed, we anticipate that there may be a number of ways that the outcome measure could be missing. These include loss to follow-up and or partial information collected at anyone study visit. A further analysis will be performed in which missing primary outcome data will be imputed. Multiple imputation will be also performed on missing covariate and outcome data for all secondary clinical analyses in a similar way to that performed for the primary analysis.

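### Days without an adherence record are not taken under the adherence ratio but missing under the missing-data section, so the same records can give two values of the primary outcome

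*Protocol article*

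**What the plan says.** Adherence assessment sets the intervention-arm measure as the "number of days the device was opened as a proportion of the total number of days in the entire period of their MDR-TB treatment", and states that "opening of the devices will be equated to a patient swallowing their medication". It deducts nothing for days on which no record exists.

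Additional analyses and handling of missing data then says of the same outcome that "we anticipate that there may be a number of ways that the outcome measure could be missing", and adds: "These include loss to follow-up and or partial information collected at anyone study visit". In the generalized estimating equations (GEE) model, "missing outcome data will be dealt with using a missing at random assumption". Also, "A further analysis will be performed in which missing primary outcome data will be imputed".

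Table 2 (Determination of TB treatment outcomes) defines loss to follow-up as an interruption of treatment lasting two consecutive months or longer. Sample size allows for 20% loss to follow-up.

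For the control arm, Control arm says of the monthly review: "At this point, the study team will record the number of doses taken/missed according to the TB card". Adherence assessment divides days attended by a total worded differently from the intervention arm's: treatment 'complaint' days, presumably meaning compliant, over the whole treatment period.

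**The concern.** Two stated rules cover the same days and disagree. Each goes wrong in one situation if followed alone.

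- **The ratio alone.** A month of openings lost with a faulty or mislaid device stays in the denominator and adds nothing to the numerator. A record failure becomes non-adherence.
- **The missing-data section alone.** A participant who stops treatment for two months or more becomes a case of missing outcome. In an adherence trial that interruption is the event being measured. Missing at random would fill it in from months and participants with data.

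It is also unclear whether the control arm follows either rule, because its denominator is worded differently. The value of the primary outcome, and possibly the comparison with the −10% margin, would then depend on which section the analyst follows.

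**Working it through.** The article gives no figure on this point, so there is none to reproduce.

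**Inputs from the article**
- Treatment length M: "9 months for participants that qualify for shorter MDR-TB/RR-TB treatment regimen and 18 months for those selected for the longer" regimen (Laboratory assessments).
- Device data are downloaded monthly (Intervention arm), so one month is a natural unit of loss.
- Good-adherence cut-off in the intervention arm: 70% (Adherence assessment).
- Loss to follow-up 20%; non-inferiority margin −10% (Sample size).

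**Step 1: one lost month, one participant.** Let r be the opening rate in the recorded months.
- Literal ratio: r(M − 1)/M.
- Month missing and filled at the participant's own rate (a simplification of missing at random): r.
- Gap: r/M, at most 1/M.

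| r | 9 months: ratio / missing / gap | 18 months: ratio / missing / gap |
|---|---|---|
| 100% | 88.9 / 100 / 11.1 | 94.4 / 100 / 5.6 |
| 90% | 80.0 / 90 / 10.0 | 85.0 / 90 / 5.0 |
| 80% | 71.1 / 80 / 8.9 | 75.6 / 80 / 4.4 |
| 70% | 62.2 / 70 / 7.8 | 66.1 / 70 / 3.9 |

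**Step 2: the cut-off.** On 9 months with one lost, the literal ratio reaches 70% only if r ≥ 0.70 × 9/8 = 78.75%. A participant between 70% and just under 78.75% in the recorded months passes under one section and fails under the other.

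**Step 3: the early comparisons.** At 2 and 6 months, one lost month moves a value by up to 1/2 = 50 and 1/6 = 16.7 points.

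**Step 4: loss to follow-up.** Take r = 90% and loss after month 4 of 9. If the entire period means planned treatment, the ratio is 0.90 × 4/9 = 40%. If later days are missing, it stays at 90%. The article does not say whether the period is planned or actual.

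**Step 5: arm level.** If a share f of an arm each lose one month of nine, the arm mean moves by f × r/9. The article gives no f; 10% to 20% is assumed.
- f = 0.10, r = 0.80: 0.9 points.
- f = 0.20, r = 1.00: 2.2 points.

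For loss to follow-up, an illustration: if the planned 20% were all lost as in Step 4, one arm's mean would differ between the two rules by 0.20 × (90 − 40) = 10 points. The timing is assumed, as is reading the 20% in the Table 2 sense.

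**Step 6: the difference between arms.** With the same rule in both arms and the same r and M, isolated lost months bias the difference by (f_MEMS − f_DOT) × r/M, taken with a negative sign. This is zero when the rates of loss are equal. The documents give neither rate.

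**The case against.** The strongest reply is that the sections are complementary: one defines the rate, the other says what to do when data for it are missing, and it refers back to how the rate is computed. On that view only a day-level coding rule is unstated, which an analysis plan or the standard operating manual could supply. It is true that the ratio never says in words that an unrecorded day is a missed dose. But as written it puts every treatment day in the denominator and credits only openings. A later document would have to depart from one of the two statements, so this is more than absent detail.

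Other parts of the reply stand and limit the point.
- Background and rationale says the device stores data for many months after battery outage, so a skipped download alone need not lose a month.
- Data collection plan gathers pill counts and self-reported missed days monthly, which can inform gaps.
- The missing-data section does not name device failure, although partial visit information would cover it.
- It also does not say that its loss to follow-up is the Table 2 category. That is the only definition the article gives.

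A reader might infer two stronger conclusions, and the documents support neither. The first is that 11 points is an error to set against the −10% margin. It is the maximum for one fully adherent participant on the shorter regimen. The second is that the bias cannot cancel because one arm uses an automatic device and the other a paper card. Different reasons for loss do not imply different rates, and neither rates nor direction are given. If the control denominator meant that unrecorded days are handled differently there, equal rates would not cancel either, but its wording is too unclear to establish that.

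**Conclusion.** The point holds as a clash between two stated rules for the primary outcome, and it should be settled before analysis. It matters most for loss to follow-up, where one rule scores an interruption as non-adherence and the other as missing at random: 40% against 90% in the worked case, if the period is planned treatment. Isolated lost months are a lesser matter, large for one participant but small for an arm on the assumed shares. No bias in the MEMS-minus-DOT difference has been shown. Its presence and direction depend on loss rates by arm and on how the control denominator is meant.

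**What to change.** Amend Adherence assessment and Additional analyses and handling of missing data together.

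1. Use one denominator, worded identically for both arms, and state whether it is planned or actual treatment days. For item 2 to work, it must run past the point where a participant stops.
2. Count days after a participant stopped or interrupted treatment as not taken, and remove them from the list of missing outcomes.
3. Class a day as not recorded only with a documented record failure: device lost or faulty with data not recoverable, or treatment card unavailable. Take these days out of numerator and denominator.
4. Run two sensitivity analyses, counting all such days as taken and then all as not taken. Use the monthly pill counts and self-report as supporting data.
5. Report the share of unrecorded days by arm.

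Item 3 still assumes that unrecorded days resemble recorded ones, so item 4 is needed. The cost is a protocol amendment with ethics approval and a reason code on the monthly form. Trial status reports a start in November 2021 and enrolment at 70%, so reasons for months already accrued must be recovered from existing records. No extra visits are needed.
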